### Trial design

The ANKLE TRIAL is designed as a prospective open randomized multi-centre trial with a one-year follow-up in which we compare three different functional treatment strategies of acute ankle sprains. A residual-free healing and prevention of chronic symptoms and functional instability will be pursued. Therefore, results during follow-up primarily will be evaluated with a statistically validated scoring scale, which measures ankle joint function in the rehabilitation phase after acute ligament injury, according to Karlsson and Peterson [25]. In this scale a maximum of 90 points can be given in following categories: pain (20), swelling (10), instability (subjective) (15), stiffnes (5), stair climbing (10), running (10), work activities (15), and use of support device (5). Selected patients will be randomized in three treatment groups, as showed [Figure 1] with an allocation ratio of 1:1:1. For follow-up patients will return to the hospital after five to seven days (baseline), after six weeks and after one year. After six months patients will be contacted by telephone [Table 1].

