**Figure 1 F1:**
[figure not shown]
**ANKLE TRIAL flow chart (inclusion, randomization and follow-up)**.

**Table 1 T1:** Follow-up moments and outcome measurement

	VAS pain	Karlsson	FAOS	VAS satisfaction	Number of recurrences
< 24 h	+	-	-	-	-

5-7 days	+	+	+	-	-

6 weeks	+	+	+	-	+

6 months	+	+	-	+	+

1 year	+	+	+	+	+

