### Participants

Adult and healthy patients with acute (within 24 h), single sided and first inversion trauma of the lateral ankle ligaments will be eligible for inclusion. Patients will be excluded if they do not master the Dutch language, if they are low ambulatory or if there is another (or secondary) diagnosis than lateral ankle sprain (e.g. fracture of the ankle). If necessary, × rays will be performed to exclude ankle fractures, according to the Ottawa ankle rules. All lateral ankle ligament injuries will be included, regardless of severity, as in the acute stage it is hard to distinguish between. After 5-7 days, following the case record form, a delayed physical examination according to Van Dijk [4] will take place and function scores according to De Bie et al. [26] will be determined. From here we can distract the severity of the injuries, which will be important for sub analysis.

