### Interventions

The first treatment group will receive pressure bandage and RICE (Rest, Ice, Compression, Elevation) therapy for 5 to 7 days followed by tape treatment for 6 weeks, the second group will be treated by pressure bandage and RICE therapy for 5 to 7 days followed by brace treatment for 6 weeks and the third group RICE therapy and purely functional treatment. The last group will not be given pressure bandage or external support, except for an elastic sock if desired.

In addition, patients in all three groups will receive the same ankle exercise schedule, based on regular existing physiotherapy protocols [Table 2]. Only the first two days after the inversion trauma patients (of all groups) are allowed to take Paracetamol for pain relieve as necessary. After two days they can start weight bearing guided by pain.

**Table 2 T2:** Stepwise exercise schedule with training modality accents per phase

	Training Modalities							
**Step**	**Time**	**N***	**Range of motion**	**Weight bearing**	**Walking**	**Stretching**	**Strength**	**Balance**

1	0-2 days	1-3	+++	minimal	-crutches	-	-	-

2	3-10 days	4-6	+	+	+ guided by pain			

3	11-21 days	7-10	++	++	++ incl running	+	+	++ one leg standing

4	3-6 weeks	11-14	++	++	++	+	++	+++

* Number of exercises

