### Randomization and blinding

Physicians at the emergency department of both Jeroen Bosch hospital, 's-Hertogenbosch, The Netherlands and Slotervaart Hospital, Amsterdam, The Netherlands will recruit patients. Using the same study protocol for both hospitals, the physician will inform patients, who meet the inclusion criteria, about the study. The selected patients will also receive a brochure with written patient information. To avoid selection bias, only after they have signed informed consent, patients will be allocated to one of the three treatment strategies using a web-based computer randomization tool. Independent and qualified plaster nurses will be responsible for follow-up and data collection of the case record forms after 5-7 days and after 6 weeks. FG will collect data out of the case record forms and will put them into a database (not blinded). SW finally will analyze this objective database.

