### Statistical analyses

Baseline characteristics will be presented using descriptive statistics; continuous data will be summarized as mean and standard deviation in case of normal distribution, or as median and range when distribution is skewed. Categorical data will be presented a frequencies and proportions.

The primary analysis will be performed on the main outcome measure of this study, the Karlsson score, at 6 months follow-up. The treatment groups will be compared using an ANOVA test with post hoc pairwise comparisons (with Bonferrini correction). The adjusted confidence intervals from these contrasts will be used to test for non-inferiority using the prespecified non-inferiority margin.

Due to the repeated datastructure, secondary analyses will be performed using linear mixed models on the Karlsson score, FAOS score and VAS scores (change from baseline) to estimate change as a function of time and mean differences between the treatment groups. Akaike Information Criteria (AIC) will be used as an indicator for model fit. The number of recurrent ankle injuries and adverse events will be analyzed using a *X*^2 ^test or log-rank test, when appropriate. Analyses will be based on the intention-to-treat principle and performed in PASW statistics 18 (SPSS Inc. Chicago, IL). Statistical uncertainty will be quantified by 95% confidence intervals.

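### The secondary mixed models are put on change from a baseline taken 5-7 days after injury, after arm-specific treatment has begun, so any first-week effect is subtracted from later Karlsson and FAOS contrasts

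*Protocol article*

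**What the plan says.** - **Analysis.** The Statistical analyses section specifies "linear mixed models on the Karlsson score, FAOS score and VAS scores (change from baseline) to estimate change as a function of time", and the same sentence gives these models the job of estimating mean differences between the arms.
- **What baseline means.** Under Trial design, "patients will return to the hospital after five to seven days (baseline), after six weeks and after one year". No other visit in the article is given that name as a time point.
- **When allocation happens.** Participants are "Adult and healthy patients with acute (within 24 h), single sided and first inversion trauma". They are recruited at the emergency department, and "only after they have signed informed consent, patients will be allocated to one of the three treatment strategies" (Randomization and blinding).
- **What happens before that visit.** Under Interventions, groups 1 and 2 have a pressure bandage with RICE for 5 to 7 days before tape or brace. Group 3 has RICE, and "The last group will not be given pressure bandage or external support, except for an elastic sock if desired".
- **What is measured when.** Table 1 ("Follow-up moments and outcome measurement") has only VAS pain at under 24 hours. Karlsson and FAOS are first taken at 5-7 days, and VAS satisfaction at 6 months. The abstract counts one week among the outcome times.
- **Primary analysis.** This is the Karlsson score at 6 months by ANOVA, and it is not described as a change score.

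**The concern.** A baseline used for subtraction should be measured before the allocated treatments can act. Here the Karlsson and FAOS baseline is measured at the end of the first treatment phase, and that phase differs between group 3 and the other two. The value is an outcome of allocation. The abstract treats it as one, while the Trial design section calls it the starting point.

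If change is computed from it, whatever the pressure bandage did or did not do in the first week is removed from every later comparison. Groups 1 and 2 have the same first-week treatment, so their mutual contrast should not be shifted systematically. The distortion falls on no support against tape or brace, which is the question in the Objective and Hypothesis sections. The mixed models are the only between-arm analysis that the article states for FAOS, for VAS, and for Karlsson at 6 weeks and 1 year.

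**Working it through.** **1. The plan's own figure.** The Sample size section gives margin 10, SD 15, expected difference 0, one-sided alpha 0.025/3 and power 80%.

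n per group = 2 × [15 × (2.394 + 0.842) / 10]² = 47.1, so 48. A t-based calculation gives 49 (alpha 0.00833) or 50 (alpha rounded to 0.008). The stated 50 is reproduced. Allowing for 15% dropout, 50/0.85 = 58.8, so 59, against the stated 60. From 60 enrolled, 60 × 0.85 = 51 per arm remain. The point below does not depend on the sample size; 51 is used only to give it a scale.

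**2. What a change contrast estimates.** Let d₁ be the mean difference (no support minus support) at 5-7 days and d_t the difference at a later visit. The difference between arms in mean change is

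(later mean − 5-7 day mean, no support) − (later mean − 5-7 day mean, support) = d_t − d₁.

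The documents give no value for d₁, so the values here are assumed, in Karlsson points:

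| d₁ | d_t | Change contrast | What the reader would see |
|---|---|---|---|
| −5 | −5 | 0 | a persisting deficit disappears |
| −5 | 0 | +5 | catch-up looks like a benefit |
| +5 | 0 | −5 | loss of an early lead looks like harm |
| +3 | +5 | +2 | a growing lead is shrunk but keeps its sign |
| 0 | −5 | −5 | no distortion |

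A 5-point first-week difference moves every later contrast by 5 points, half the 10-point margin.

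**3. How often this would mislead.** Assume SD 15 at both visits (the plan gives one SD, for planning), 51 per arm, within-patient correlation ρ of 0.3 to 0.5, d_t = 0 and d₁ of 5 points in either direction.

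SE of the change contrast = 15 × √(2(1 − ρ)) × √(2/51)

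- ρ = 0.3: 15 × 1.183 × 0.198 = 3.51. Then 5/3.51 = 1.42, and P(95% CI excludes 0) = Φ(1.42 − 1.96) + Φ(−1.42 − 1.96) = 0.296.
- ρ = 0.5: 15 × 1 × 0.198 = 2.97. Then 5/2.97 = 1.68, and the probability is 0.391.

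With no bias the figure would be 5%.

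**4. VAS.** VAS pain has an under-24-hour value that could serve as baseline. The analysis section does not say whether that value or the 5-7 day value is meant. VAS satisfaction has no value before 6 months, so change from baseline cannot be computed for it.

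**The case against.** **The analysis is only secondary.** This stands. The confirmatory non-inferiority test uses the 6-month Karlsson score with no subtraction. A reader might infer that the trial's main conclusion is compromised; the documents do not support that.

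**The parenthesis may be shorthand.** The sentence says that models are fitted on the scores because the data are repeated, so it could mean that observed scores are modelled and change is only the time contrast. The first-week effect would then be recoverable. That change from baseline cannot apply to VAS satisfaction also suggests loose wording. This reading is possible, but it is not what change from baseline plainly says, and the article does not state it. The parenthesis might also attach to VAS alone. In that case Karlsson and FAOS escape, and VAS pain is at fault only if its baseline is the 5-7 day value, which the text leaves open.

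**Tape and brace start at that visit.** This may explain the label. But allocation comes earlier, and the abstract defines groups 1 and 2 as pressure bandage with tape or brace, so the first week belongs to the strategies compared.

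**No first-week difference is shown.** Correct. A reader might infer that the arms already differ in score at 5-7 days. Only the treatment is documented to differ.

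**Two further readings go too far.** One is that an arm doing better in week one must look worse later. That requires its advantage to shrink; a stable advantage gives zero and a growing one keeps its sign. The other is that patients who miss the 5-7 day visit are lost, against intention to treat. That follows only from literal subtraction, and the article states no rule for missed visits.

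**Conclusion.** The point holds for the secondary mixed models, as a should-fix. On the plain reading, Karlsson and FAOS changes are taken from a post-allocation value, and the contrast of no support with tape or brace becomes the later difference minus the 5-7 day difference. That identity needs no assumption.

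The size does need assumptions. The bias equals the first-week difference point for point and is zero if that difference is zero. A 5-point difference would give a falsely significant difference in change in about 30% to 39% of trials, under SD 15 at both visits, 51 per arm, correlation 0.3 to 0.5 and no later difference. None of this reaches the primary 6-month ANOVA or the sample size. For VAS pain the point is conditional on which value is the baseline.

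**What to change.** Before analysis, amend the wording as follows.

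1. Call the 5-7 day visit the first follow-up.
2. For Karlsson and FAOS, fit the mixed models to the observed scores at every scheduled visit, 5-7 days included, with arm-by-visit contrasts. Neither subtract nor adjust for the 5-7 day value. Adjustment would still remove part of a first-week effect: with equal SDs the regression slope equals ρ, so a 5-point difference would shift the contrast by 0.3 × 5 = 1.5 to 0.5 × 5 = 2.5 points.
3. For VAS pain, state that the under-24-hour value is the baseline covariate, after confirming that it is taken before allocated treatment starts, and treat 5-7 days onward as outcomes.
4. Analyse VAS satisfaction at 6 months and 1 year without change from baseline.

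The cost is a change of wording and one check on the timing of the first VAS pain reading. All the measurements are already in Table 1, and the sample size does not change.

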## Discussion

The ANKLE TRIAL is a randomized controlled trial in which a purely functionally treated (control) group, without any form of external support, will be investigated and compared with two external support treatment (intervention) groups. Recruitment of patients in Jeroen Bosch Hospital has started since January 2010 and in Slotervaart Hospital since July 2011. Recruitment will be finished when 180 patients have been included, which we expect will be at the end of 2011. We expect to publish initial results of our study in 2013.

### Impact of results

The results of this study can lead to a changing view on treatment of ankle sprains. Currently a new guideline concerning treatment of acute ankle sprain has been introduced in The Netherlands, based on latest insights from the literature [29]. The developers of this guideline concluded that rehabilitation of athletes after acute inversion injury of the ankle should consist of varied exercises, which will improve propriocepsis, strength and coordination as well as maintaining function of the extremity.

Furthermore, a brace or tape was recommended in the (sub) acute phase following the diagnosis of acute ankle ligament injury. Also they stated that there is room for tape processing in a (top) sport population, although based on the literature it was not clear which strategy was best. To our knowledge, usefulness of any kind of external support has never been compared to a purely functional treatment without external support [9].

